### Criteria for discontinuing or modifying allocated interventions {11b}

Discontinuation of the intervention will be in the presence of worsening disease condition, upon participant request, or in the presence of any adverse effect.

### Strategies to improve adherence to interventions {11c}

As a strategy to improve adherence, a booklet was designed for this study with instructions, and exercises will be provided to the patients as well as an audio that will be sent to their cell phones using the WhatsApp application. The pelvic floor therapist will be given a mobile number with a WhatsApp account so they can send audios and contact patients to reinforce instructions for performing PFME at home. Patients will receive a WhatsApp message once a week to remind them about the exercises. A closer contact with the therapist may increase patients’ self-efficacy and adherence to the treatment [16]. In addition, patients will receive a diary to register the days when they exercise their pelvic floor in order to check adherence to home-based exercises.

### Relevant concomitant care permitted or prohibited during the trial {11d}

Patients can take institutional routine care, including, if necessary, adjuvant chemoradiotherapy. Only patients of the control group will not be allowed to receive pelvic floor physiotherapy during the study period.

### Provisions for post-trial care {30}

After completing the follow-up time (3 months) and final evaluations, patients of the control group will be invited to receive 5–10 sessions of pelvic floor rehabilitation. No compensation is offered to those who might suffer from harm from trial participation. However, we are negotiating an insurance contract to better protect patients.

### Outcomes {12}

Evaluations will take place at baseline (T1), around 3–5 weeks before stoma removal and before rehabilitation (T2), immediately after rehabilitation (T3), 3 months (T4), and 1 year after rehabilitation (T5).

The primary outcomes are the mean score of bowel symptoms and the mean score of anorectal function. The primary time point will be 3 months after finishing pelvic floor rehabilitation treatment.

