#### Main outcome: bowel symptoms

The International Consultation on Incontinence Questionnaire Anal Incontinence Symptoms and Quality of Life Module (ICIQ-B) assess fecal incontinence symptoms (including gas incontinence) and its impact on quality of life. It is separated in three domains with scores from 1 to 21 for bowel patterns, 0–28 for bowel control, and 0–26 for quality of life related to bowel symptoms [22, 23]. It was developed in the UK but still does not have a Spanish version. Its English version has shown to be robust and psychometrically solid, considering analysis of content, construct, criterion validity, internal consistency, and reliability [22, 23]. The questionnaire is in the process of translation to Chilean Spanish and validation by the authors of this study.

In addition, we will use LARS score which is a short questionnaire that has been useful for measuring the impact of intestinal sequelae on the quality of life of patients following sphincter preserving rectal cancer surgery [8]. The LARS score was developed based on a Danish cohort of 961 patients 27 and evaluates incontinence for flatus, incontinence for liquid stools, clustering, and urgency. The score ranges from 0 to 42 and is divided into 0 to 20 (no LARS), 21 to 29 (minor LARS), and 30 to 42 (major LARS). This score has been validated in Spanish [24].

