#### Secondary outcomes: anorectal function, quality of life, and pelvic floor muscle function

High-resolution anorectal manometry will be used to assess the maximal resting pressure, maximal squeeze pressure, rectal capacity (maximal tolerable volume), and rectal sensitivity (initial sensation threshold). We will use high-resolution anorectal manometry with a 24-channel water-perfused catheter (Multiplex, Alacer, Biomedica, Sao Paulo, Brazil). This equipment is a low-cost water perfused system which has proven to be adequate for clinical use [25, 26]. According to a previous study, we will define effective improvement as > 15% in the anorectal manometry parameters [9]. This test will be performed by a trained physician.

Quality of life will be evaluated with the validated and widely used instrument of the European Organization for Research and Treatment of Cancer Quality of Life Group (EORTC), the Quality of Life Questionnaire Core-30 (QLQ-C30), and QLQ-CR29 [27–30]. A detailed manual will be used to score each question [31].

Pelvic floor muscle strength will be measured by anal palpation and graded on the Oxford Modified Scale from 0 (no contraction) to 5 (strong). This is the most widely used evaluation on pelvic floor physiotherapy [32].

Adherence to home-based pelvic floor muscle exercises will be measured with an exercise diary. We will record the number of days per week patients performed the exercises following the instructions of the physical therapist. Furthermore, we will record attendance to rehabilitation sessions.

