### Sample size {14}

The hospital carries out around 50 rectal cancer surgeries per year. The sample size calculation was performed considering the results of a previous pilot study with 10 participants with rectal cancer undergoing pelvic floor rehabilitation [33]. The study used the ICIQ-B and reported results in the domain bowel control after rehabilitation [mean of rehabilitation group = 2.8 (SD = 2.8) and mean of rehabilitation group = 4.9 (SD = 5.7)]. These values were introduced at an online sample size calculator [34] with a power of 80%, alpha 0.05, and an enrollment ratio of 1/1, resulting in an estimated sample size of 56 participants. Then, considering the need of exclusion due to clinically relevant anastomotic leakage, which has been estimated around 10.9% of the cases [35], we will require a total of 62 patients, 31 in each group.

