## Statistical methods

### Statistical methods for primary and secondary outcomes {20a}

Data will be maintained in printed questionnaires which will be registered on an Excel dataset. A monitor will check the completeness of data and rigorously control patient’s follow-up. Data will be analyzed with descriptive (mean, standard deviation, median, interquartile range, and frequencies) and inferential statistics at the program SPSS®. A normality test will be performed using Kolmogorov-Smirnov criteria. For variables which follow normality criteria, we will use an independent T test to compare groups. In the case of a non-normal distribution, we will use the Mann-Whitney U test. To compare variables between pre- and post-intervention, we will use a paired T test or a Wilcoxon test. A significance threshold of *p* < 0.05 will be adopted for all tests.

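### The protocol article contradicts itself on which outcomes are primary, and does not say which variable its primary mean scores refer to

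*Protocol article*

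**What the plan says.** The article ranks the outcomes in three places, and the rankings differ.

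- **Outcomes {12}, opening text:** "The primary outcomes are the mean score of bowel symptoms and the mean score of anorectal function". The time point is fixed: "The primary time point will be 3 months after finishing pelvic floor rehabilitation treatment" (T4).
- **Outcomes {12}, sub-headings:** the first reads "Main outcome: bowel symptoms" and the next reads "Secondary outcomes: anorectal function, quality of life, and pelvic floor muscle function".
- **Abstract, Methods:** ICIQ-B, manometry, Oxford-scale muscle strength and EORTC QLQ-C30 are all listed as main outcome measures.

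The variables under these labels are as follows.

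- **Bowel symptoms:** the ICIQ-B has no total score in the text. "It is separated in three domains with scores from 1 to 21 for bowel patterns", with bowel control (0–28) and bowel-related quality of life (0–26) as the other two. The LARS score (0–42) is added under the same heading: "In addition, we will use LARS score".
- **Anorectal function:** maximal resting pressure, maximal squeeze pressure, rectal capacity and rectal sensitivity. The same paragraph also defines effective improvement as a change above 15% in the manometry parameters.

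Statistical methods {20a} sets one threshold: p < "0.05 will be adopted for all tests". Sample size {14} uses pilot data that "reported results in the domain bowel control after rehabilitation", and no other variable.

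**The concern.** Which outcome is primary decides what counts as a positive trial. As written, a significant manometry result could be presented as primary success by citing the opening sentence of Outcomes {12}. A null manometry result could be set aside by citing the sub-heading below it. The choice could be made after the data are seen.

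The primary sentence also leaves open which ICIQ-B domain, or which manometry parameter, carries the claim. With every test at 0.05, the chance of some false-positive primary result depends on how many variables are eligible and on whether one success is enough. The planned power applies to only one of them.

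**Working it through.** **1. The plan's own figure.** Inputs from Sample size {14}: means 2.8 and 4.9 (difference 2.1), SDs 2.8 and 5.7, alpha 0.05, power 80%, 1:1 allocation. Two-sided testing is assumed because sidedness is not stated.

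Per arm, n = 2 × (1.960 + 0.842)² × SD² / difference².

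- With SD 2.8: 2 × 7.849 × 7.84 / 4.41 = 27.9, so 28 per arm and **56 in total**. This reproduces the stated figure for one variable tested once at 0.05.
- With both SDs: 7.849 × (2.8² + 5.7²) / 4.41 = 7.849 × 40.33 / 4.41 = 71.8, so 72 per arm and 144 in total. Power at 56 is then about 42%.

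**2. How many variables could be called primary at T4.**

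- Opening sentence of Outcomes {12}: 3 ICIQ-B domains + 1 LARS score + 4 manometry parameters = 8. Leaving out the ICIQ-B quality-of-life domain gives 7.
- Sub-heading hierarchy (bowel symptoms only): 3 + 1 = 4, or 3 without the quality-of-life domain.
- One variable for each of the two named outcomes: 2.

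**3. Chance of at least one false positive, if any single significant result counts as success.** For k independent tests this is 1 − 0.95^k.

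- k = 2: 1 − 0.9025 = 9.8%
- k = 3: 1 − 0.8574 = 14.3%
- k = 4: 1 − 0.8145 = 18.5%
- k = 7: 1 − 0.6983 = 30.2%
- k = 8: 1 − 0.6634 = 33.7%

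These outcomes will be correlated, but the article gives no correlations. The table assumes one common correlation among two-sided z tests (simulation, 400,000 draws).

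| Tests | 0.3 | 0.5 | 0.7 | 0.9 |
|---|---|---|---|---|
| 2 | 9.5% | 9.1% | 8.4% | 7.0% |
| 4 | 17.4% | 15.6% | 13.0% | 9.3% |
| 8 | 30.0% | 25.0% | 19.2% | 11.9% |

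**4. Cost of keeping two primaries.** At alpha 0.025 each, with the difference of 2.1 and SD 2.8, power at 56 falls from 80% to 71%. The total needed for 80% rises to 68 before the allowance for leakage exclusions.

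**The case against.** Several points on the other side are sound.

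- **Mean score may not mean a composite.** A reader might infer that the article promises two composite scores that do not exist. The phrase can equally mean the group mean of a scale, and each ICIQ-B domain has such a mean. What stands is narrower: the sentence does not say which domain or parameter counts.
- **There is a hierarchy, and each test is controlled.** A reader might infer that the plan has no error control at all. The sub-headings do rank the outcomes, and each test is held at 5%. What is not stated is familywise control, and the ranking is contradicted a few lines earlier.
- **Eight is a ceiling.** It requires the opening sentence to override the sub-heading, the LARS score to be primary rather than supportive, and a quality-of-life domain to count as a bowel symptom. Under the sub-headings the count is three or four.
- **The article states no rule that one success is enough.** If every primary had to succeed, the error would not be inflated. It states no all-must-succeed rule either, so the question is open.
- **A statistical analysis plan could add detail.** It could settle the multiplicity method. It could not agree with both labels for anorectal function, and which outcome is primary is a protocol decision.
- **ICIQ-B bowel control is not the only candidate.** The article says the Chilean Spanish ICIQ-B is still being translated and validated, whereas the LARS score is validated in Spanish. That is a fair argument about which variable to name, and it does not remove the need to name one.

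**Conclusion.** The contradiction is plain in the current text and must be resolved: anorectal function is both primary and secondary, and the abstract gives a third list. The primary variable is not identified, all tests share one unadjusted threshold, and the sample size covers one ICIQ-B domain.

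The size depends on the reading. If any one significant result could be claimed as primary success, independent tests give about 10% for two outcomes, 14% to 19% for three or four bowel variables, and at most 34% for all eight. With assumed common correlations from 0.3 to 0.9, the eight-test figure runs from about 30% down to 12%. A reader might take 34% as the trial's false-positive rate. The document does not support that, because the figure needs the widest count, independence and an unstated one-success rule.

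Two further inferences should be avoided. The pilot values are described only as measured after rehabilitation, so they are not shown to be values at T4. The stated 80% power for bowel control is not secure either, because 56 reproduces only with the smaller of the two SDs.

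**What to change.** 1. In Outcomes {12}, name one primary variable at T4, compared between arms at two-sided 0.05. The ICIQ-B bowel control domain (0–28) is the natural choice because the sample size was built on it. If the LARS score is preferred because it is already validated in Spanish, the sample size must be redone for it.
2. Remove anorectal function from the primary sentence, so that it agrees with the sub-heading that makes it secondary.
3. Rewrite the abstract's list of main outcome measures to match.
4. List the other ICIQ-B domains, the LARS score and the four manometry parameters as secondary, including the criterion of more than 15% improvement. Report them with confidence intervals and without a primary claim.
5. If a manometry parameter is to stay co-primary, name that single parameter and apply Holm across the two.

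**Cost.** This is a change of wording plus notice to the ethics committee and the registry, which the article already provides for when outcomes change. Trial status says recruitment has not started. The investigators give up the option of claiming success on manometry or another domain alone. Naming bowel control leaves the number of patients unchanged on the SD of 2.8 that reproduces 56, but the choice of SD should be checked separately before 80% power is quoted for it. Under Holm, the first step is at 0.025, with the loss of power shown in the working.

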#### Main outcome: bowel symptoms

The International Consultation on Incontinence Questionnaire Anal Incontinence Symptoms and Quality of Life Module (ICIQ-B) assess fecal incontinence symptoms (including gas incontinence) and its impact on quality of life. It is separated in three domains with scores from 1 to 21 for bowel patterns, 0–28 for bowel control, and 0–26 for quality of life related to bowel symptoms [22, 23]. It was developed in the UK but still does not have a Spanish version. Its English version has shown to be robust and psychometrically solid, considering analysis of content, construct, criterion validity, internal consistency, and reliability [22, 23]. The questionnaire is in the process of translation to Chilean Spanish and validation by the authors of this study.

In addition, we will use LARS score which is a short questionnaire that has been useful for measuring the impact of intestinal sequelae on the quality of life of patients following sphincter preserving rectal cancer surgery [8]. The LARS score was developed based on a Danish cohort of 961 patients 27 and evaluates incontinence for flatus, incontinence for liquid stools, clustering, and urgency. The score ranges from 0 to 42 and is divided into 0 to 20 (no LARS), 21 to 29 (minor LARS), and 30 to 42 (major LARS). This score has been validated in Spanish [24].

#### Secondary outcomes: anorectal function, quality of life, and pelvic floor muscle function

High-resolution anorectal manometry will be used to assess the maximal resting pressure, maximal squeeze pressure, rectal capacity (maximal tolerable volume), and rectal sensitivity (initial sensation threshold). We will use high-resolution anorectal manometry with a 24-channel water-perfused catheter (Multiplex, Alacer, Biomedica, Sao Paulo, Brazil). This equipment is a low-cost water perfused system which has proven to be adequate for clinical use [25, 26]. According to a previous study, we will define effective improvement as > 15% in the anorectal manometry parameters [9]. This test will be performed by a trained physician.

Quality of life will be evaluated with the validated and widely used instrument of the European Organization for Research and Treatment of Cancer Quality of Life Group (EORTC), the Quality of Life Questionnaire Core-30 (QLQ-C30), and QLQ-CR29 [27–30]. A detailed manual will be used to score each question [31].

Pelvic floor muscle strength will be measured by anal palpation and graded on the Oxford Modified Scale from 0 (no contraction) to 5 (strong). This is the most widely used evaluation on pelvic floor physiotherapy [32].

Adherence to home-based pelvic floor muscle exercises will be measured with an exercise diary. We will record the number of days per week patients performed the exercises following the instructions of the physical therapist. Furthermore, we will record attendance to rehabilitation sessions.

For descriptive purposes, we will use the hospital register of socio-demographic and health-related information, including the following variables: age in years; schooling; self-reported ethnicity; marital status; profession; working status before cancer diagnosis; self-reported comorbidities (diabetes, hypertension, depression, asthma, COPD, smoking, and alcohol consumption); physical activity during leisure time; heart rate, blood pressure; use of anti-motility or anti-diarrhea agents; type of cancer; stage; treatments received (surgery, radiotherapy, chemotherapy, immunotherapy); and body weight, height, and body mass index. SPIRIT guidance: primary, secondary, and other outcomes, including the specific measurement variable (e.g., systolic blood pressure), analysis metric (e.g., change from baseline, final value, time to event), method of aggregation (e.g., median, proportion), and time point for each outcome. Explanation of the clinical relevance of chosen efficacy and harm outcomes is strongly recommended.

### Participant timeline {13}

Participant timeline is summarized in SPIRIT (Fig. 2).

**Fig. 2 Fig2:**
[figure not shown]
SPIRIT schedule of enrollment, intervention, and assessment

### Sample size {14}

The hospital carries out around 50 rectal cancer surgeries per year. The sample size calculation was performed considering the results of a previous pilot study with 10 participants with rectal cancer undergoing pelvic floor rehabilitation [33]. The study used the ICIQ-B and reported results in the domain bowel control after rehabilitation [mean of rehabilitation group = 2.8 (SD = 2.8) and mean of rehabilitation group = 4.9 (SD = 5.7)]. These values were introduced at an online sample size calculator [34] with a power of 80%, alpha 0.05, and an enrollment ratio of 1/1, resulting in an estimated sample size of 56 participants. Then, considering the need of exclusion due to clinically relevant anastomotic leakage, which has been estimated around 10.9% of the cases [35], we will require a total of 62 patients, 31 in each group.

### Recruitment {15}

Recruitment will be performed by the coloproctologist surgeons of the institution who will provide a referral for the study for those patients that comply with eligibility criteria.

## Assignment of interventions: allocation

### Sequence generation {16a}

The allocation of participants to groups will be randomized using computer-randomized allocations prepared by an independent person. Sequence generation will be performed in blocks of 10.

### Concealment mechanism {16b}

Allocation concealment will be guaranteed with sealed opaque envelopes.

### Implementation {16c}

The allocation sequence will be generated by an independent statistician. After screening for eligibility, the participants will be allocated to the next available allocation by the enrolling researcher using sealed and numbered envelopes. The therapist performing the treatments of the intervention group will assign participants to interventions.

## Assignment of interventions: blinding

### Who will be blinded {17a}

The people assessing the outcomes and those analyzing the results/data will be blinded.

### Procedure for unblinding if needed {17b}

Not applicable.

## Data collection and management

### Plans for assessment and collection of outcomes {18a}

One of the researchers, a physical therapist specialized in cancer rehabilitation, will be responsible for contacting patients to assess outcomes at baseline and at follow-up visits. All included questionnaires are validated. Anorectal manometry will be performed by another of the researchers, a physician well-trained in the technique.

### Plans to promote participant retention and complete follow-up {18b}

Patients will receive a WhatsApp message once a week to remind them about the exercises. In case they do not use this app, the therapist will call them once a month. A closer contact with the therapist may increase patients’ self-efficacy and adherence to the treatment [16].

### Data management {19}

Data will be tabulated in an Excel sheet anonymously using codification by a research assistant. Control and experimental group will be coded anonymously with numbers (1, 2) aiming to blind the person who will perform statistical analysis. Data will be stored in the secured network of Universidad Bernardo O´Higgins with access to the researchers and, for security reasons, in an external hard drive which will be used to back up regularly the database. The data monitoring team will be the researcher that assesses outcomes and another responsible for data analysis.

### Confidentiality {27}

Personal information will be maintained only by the therapist in a special folder stored at the institution where data will be collected.

### Plans for collection, laboratory evaluation, and storage of biological specimens for genetic or molecular analysis in this trial/future use {33}

Not applicable because there are no biological specimens in this study.

## Statistical methods

### Statistical methods for primary and secondary outcomes {20a}

Data will be maintained in printed questionnaires which will be registered on an Excel dataset. A monitor will check the completeness of data and rigorously control patient’s follow-up. Data will be analyzed with descriptive (mean, standard deviation, median, interquartile range, and frequencies) and inferential statistics at the program SPSS®. A normality test will be performed using Kolmogorov-Smirnov criteria. For variables which follow normality criteria, we will use an independent T test to compare groups. In the case of a non-normal distribution, we will use the Mann-Whitney U test. To compare variables between pre- and post-intervention, we will use a paired T test or a Wilcoxon test. A significance threshold of *p* < 0.05 will be adopted for all tests.

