## Introduction

### Background and rationale {6a}

Rectal cancer is a recognized health problem that compromises patients’ health-related quality of life. Worldwide in 2018, the incidence of rectal cancer was 3.9%, while its mortality rate was 3.2%, considering the total number of cancer cases [1]. Nevertheless, the prevalence of rectal cancer survivorship is increasing with the improvement of treatments, and surgery with radio-chemotherapies has significantly improved oncological outcomes [2]. In addition, the implementation of perioperative optimized protocol pathways has reduced rates of morbidity, improved recovery, and shortened the length of hospital stay [3].

Currently, surgeries for rectal cancer are less aggressive and try to preserve the anal sphincter and to avoid permanent ostomies [2]. Nevertheless, the partial or total loss of the rectal reservoir and its replacement with the remaining colon is associated with functional sequelae [4], triggering a negative effect on the pelvic floor region with compromises in evacuation and urinary function. This has been recently investigated and termed as “low anterior resection syndrome” (LARS) [4, 5].

LARS includes a set of symptoms, as well as frequent bowel movements, urgency, fecal incontinence, and disordered evacuation. It was estimated that this syndrome occurs in 70 to 90% of patients [4, 5]. Studies have shown that the main risk factors for developing LARS after surgery are radiotherapy and tumor height, which both have a negative impact on bowel function [6, 7]. LARS can show improvement over the first 2 years, but symptoms persist for longer than 2 years in nearly 60% of patients [8].

There are few studies testing interventions to improve bowel symptoms in patients treated for colorectal cancer, especially those who are submitted specifically to sphincter saving surgeries which are associated with LARS. One retrospective study showed the benefits of biofeedback with balloon rectal training on bowel function, measured with questionnaires and an anorectal manometry [9]. Another recent prospective study included patients who experienced fecal incontinence after sphincter-saving surgery and showed that electrical stimulation and biofeedback improved maximal squeeze pressure and stool frequency and diminished the use of antidiarrheal medications [10].

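### A normality test chooses between an unadjusted t test and Mann-Whitney for the primary comparison, which does not match the mean-score outcome and leaves the collected baseline score unused

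*Protocol article*

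**What the plan says.** All references are to the protocol article.

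- **Choice of test** (Statistical methods {20a}): "A normality test will be performed using Kolmogorov-Smirnov criteria". Then "For variables which follow normality criteria, we will use an independent T test to compare groups", and "In the case of a non-normal distribution, we will use the Mann-Whitney U test".
- **Use of earlier values** (same section): "To compare variables between pre- and post-intervention, we will use a paired T test or a Wilcoxon test". This comparison is separate from the one between groups, for which no covariate is named.
- **Target** (Outcomes {12}): "The primary outcomes are the mean score of bowel symptoms and the mean score of anorectal function", with the primary time point 3 months after rehabilitation (T4). The same section schedules a baseline assessment, T1, which the abstract places before surgery.
- **Planning** (Sample size {14}): ICIQ-B bowel control with means 2.8 (SD 2.8) and 4.9 (SD 5.7), giving 56 participants. The bowel control domain runs from 0 to 28.
- **Prognosis** (Background {6a}): "the main risk factors for developing LARS after surgery are radiotherapy and tumor height". Radiotherapy is among the treatments recorded for descriptive purposes. Tumour height is not in that list. Patients with neoadjuvant chemoradiotherapy are eligible, and adjuvant treatment is permitted.
- **Randomisation** ({16a}): "Sequence generation will be performed in blocks of 10". No stratification factor is stated.

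**The concern.** Two features of the fixed analysis work against the trial's own aim.

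First, the two branches of the rule answer different questions. The t test addresses a difference in means, which is what the outcome definition names and the sample size assumes. Mann-Whitney addresses whether scores in one arm tend to exceed those in the other. With skewed scores of unequal spread the two can disagree, and the main p-value may then not refer to the effect for which the trial was sized.

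Second, the T1 score is measured but plays no part in the group comparison, and the same holds for radiotherapy given before randomisation. Using them costs almost nothing and can only be expected to help precision, by an amount the documents do not let anyone fix.

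**Working it through.** **1. Reproduce the stated sample size.** Inputs: difference 4.9 - 2.8 = 2.1, power 80%, alpha 0.05 (two-sided assumed), ratio 1:1.

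n per arm = 2 × (1.960 + 0.842)² × (SD/2.1)². With SD 2.8 in both arms this is 2 × 7.849 × 1.778 = 27.9, so 28 per arm and 56 in total. The stated figure is reproduced, and it is a calculation for a difference in means. It matches only with the smaller SD in both arms.

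**2. t-test power with both quoted SDs, 28 per arm.** SE = √[(2.8² + 5.7²)/28] = √(40.33/28) = 1.20. z = 2.1/1.20 = 1.75. Power = Φ(1.75 - 1.96) = 42%.

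**3. What the planning values say about shape.** SD/mean is 2.8/2.8 = 1.0 and 5.7/4.9 = 1.16. Normal distributions with these values would put Φ(-1.0) = 16% and Φ(-0.86) = 19% of patients below zero, which the scale does not allow. The scores must be right-skewed. The variance ratio is (5.7/2.8)² = 4.1.

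**4. What the rule would then do.** Simulation, 3,000 runs, 28 per arm. Assumptions: gamma scores with the stated means and SDs, rounded and capped at 28; Kolmogorov-Smirnov test in its Lilliefors form on the pooled data.

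| Scenario | Normality rejected | Planned rule, p < 0.05 | t test, p < 0.05 |
|---|---|---|---|
| Means 2.8 and 4.9, SDs 2.8 and 5.7 | about 100% | 24% | 41% |
| Means both 4.0, SDs 2.8 and 5.7 | about 100% | 36% | 8% |
| Both arms mean 4.9, SD 5.7 | about 100% | 4.5% | 4.2% |

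Monte Carlo error on the 36% is √(0.36 × 0.64/3000) = 0.9 points. A repeat with another seed gave 34% against 7% in the second row. The article does not say which form of the Kolmogorov-Smirnov test is meant. With the uncorrected form the gate fired in about 93% of runs in the first scenario. In the second, the repeat had it firing in 76%, with the rule rejecting in 28%.

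The first row shows that the rule would in practice be a Mann-Whitney test, with less power here than the test of means. The second shows it rejecting often when the means are equal. The third shows that it holds its level when the two distributions are identical.

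**5. What baseline adjustment could add.** Adjusting for a covariate with correlation r to the T4 score multiplies the residual variance by 1 - r² (taken as equal in both arms), so z becomes 1.75/√(1 - r²). The documents give no r, so all values are assumed.

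| r | 1 - r² | Power at 28 per arm, both SDs |
|---|---|---|
| 0 | 1.00 | 42% |
| 0.1 | 0.99 | 42% |
| 0.2 | 0.96 | 43% |
| 0.3 | 0.91 | 45% |
| 0.5 | 0.75 | 52% |

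If SD 2.8 held in both arms, 80% would become 82% at r = 0.2, 84% at 0.3 and 90% at 0.5.

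**The case against.** The best defence is that nothing here is invalid. Under 1:1 randomisation an unadjusted comparison is unbiased, and its error rate already allows for chance imbalance. Adjustment is a matter of efficiency, and the gain may be slight: resection, stoma and stoma reversal all lie between T1 and T4, so a low correlation is plausible. The section also promises means and SDs descriptively, so group means would still be reported whichever test is used. All of this stands. It limits the precision argument, but it does not reconcile a rank test with a mean outcome.

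A reader might infer more than the documents support:

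- *That the pre-test inflates type I error.* With identical distributions the rule rejected in about 4.5% of runs.
- *That the normality test is too weak at this size to matter.* Under the skew implied by the planning values it fires in most runs or nearly all.
- *That imbalance in irradiated patients is likely.* The documents give no proportion irradiated. Assuming 30-70%, a gap of 6 or more patients between arms of 28 arises in about 11-14% of trials. Small gaps are common and large ones are not.
- *That randomisation is known to be unstratified.* The article states only the block size and may leave stratification factors to the full protocol.
- *That the 42% power is a consequence of this analysis.* It follows from the two SDs in the sample size section, which is a separate matter. It serves here only as a starting point for the adjustment gain.

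**Conclusion.** The point holds in a limited form. The article itself fixes the method, so this is not a detail left to an unseen analysis plan. The gated test does not match the mean-score outcome or the sample size calculation. On the trial's own planning values the rank branch would probably be used, and it can reject when means are equal but spreads differ: about 36% against 8% for the t test, under the assumed gamma scores. The exact percentages depend on that assumption and on the form of the normality test. The direction follows from an SD at or above the mean and a variance ratio of about 4.

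Leaving out the T1 score forgoes precision of unknown size, from practically nothing at r = 0.1 to about 10 points of power at r = 0.5 with both SDs. The documents do not support calling the unadjusted comparison biased or invalid. This is a change that should be made, not a fatal flaw.

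**What to change.** Delete the Kolmogorov-Smirnov gate from the statistical methods section and pre-specify one analysis:

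- For each continuous primary score, fit a linear model (ANCOVA) of the T4 value on arm and the T1 value of the same score.
- Add radiotherapy given before randomisation (yes/no). Record it separately from adjuvant radiotherapy, which comes after randomisation and should not be a covariate. The present list of variables does not make that split.
- Add tumour height only if it is available in the record, since it is not among the listed variables.
- Report the adjusted mean difference with a 95% CI, using heteroscedasticity-robust or bootstrap standard errors.
- Keep Mann-Whitney as a sensitivity analysis.
- Use the same model for continuous secondary scores, but not for the ordinal 0-5 Oxford scale, which needs a rank or ordinal method.

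Which bowel and manometry scores count as primary is a separate question, and this wording does not settle it.

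The cost is a change of text, slightly more analysis work and at most three degrees of freedom: with 56 patients, 54 residual degrees of freedom become 51 if all three covariates are used. According to the trial status section recruitment had not begun, so the change can be made before any outcome data exist.
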